	** Study period**					
	**Enrolment**	**Allocation**	**Post allocation**			**Close- out**
**Time point**	**-t** _1_	**0**	**t** _1_	**t** _2_	**t** _3_	**t** _x_
**Enrolment**	X					
Eligibility screen	X					
Informed consent	X					
Medical history	X					
Safety index	X					
FSH, LH, Prolactin, MDA Testosterone, TAC level	X					
Semen analyses Allocation	X					
		X				
**Intervention**						
Carob group		↔				
Vitamin E group			X	X	X	
**Assessments:**						
FSH,LH,Prolactin, MDA Testosterone, TAC level						X
Semen analyses						X
**Adverse events**			X	X	X	X

**Data Monitoring: **Two researchers from BUMS not involved in the study and chosen by the university will monitor the data and supervise the conduct of the study.

**Intervention: **Patients will be assigned (1:1) to receive Carob syrup twice a day or vitamin E (comparison group) 100 mg once a day for 3 months. The Carob pods will be purchased from herbal market in Tehran and after identification and confirmation by botanist will be powdered and extracted by decoction in water (100 gram Carob, (traditional dosage) in 500 ml water). Then, after filtration, will be mixed with 500 ml USP syrup. Each patient will use 15 ml of Carob syrup/day (divided ×2) (~ dosage in traditional medicine). For all patients, a spermogram is performed first. Three months after the treatment, the spermogram and blood samples were taken from the two groups. The main consequence of the study is to improve the spermogram test and the secondary outcome of each of the parameters of prolactin, FSH, TAC, MDA and testosterone. During the initial visit where recruitment of the study occurs, the participants will be prescribed the medication. It is initially prescribed for two weeks. One week later, a telephone interview will be conducted to review the side effects and arrange an early appointment with the patient’s request. Two weeks later, the patient will received the remaining medications and adherence to treatment will be assessed (Figure 1).

**Follow-up: **Participants will be monitored monthly for signs or symptoms of adverse effects. One month later, the participants will be reviewed in the clinic and a possible side effect check list will be conducted. To prevent attrition and to assess adherence to treatment, telephone interviews will be conducted again at 2 months from administration of the drug. 3 months after intervention and upon completion of the drugs, all participants will be checked in the infertility clinic, semen analysis will be performed according to the standard clinic protocols for the sperm count, motility and morphology and serum samples will also be collected in order to evaluate markers of oxidative stress and reproductive hormones (Figure 1).

**Figure 1 F1:**
[figure not shown]
Flowchart of the study

**Adherence: **Self-assessment patient’s checklist will be used to assess adherence to treatment, also participants will instruct to bring their Carob syrup bottle each visit.

**Outcome measures: **The primary outcome measure will be the change in semen parameters after 3 months in men who were receiving Carob syrup compared to men who were taking vitamin E. Primary outcome measure according to (WHO) methodologies.

 [Time frame: Before treatment and after 3 months treatment were finished in 2 treatment arms, semen analysis will be performed]. 

sperm concentration, 2) percent motility, 3) sperm morphology Secondary outcome measures will include the change in endocrine parameters, stress oxidative markers and assessment of the adherence to treatment.

Changes in serum levels of reproductive hormones after treatment ( Time frame: Before treatment and after 3 month treatments were finished in 2 treatment arms, reproductive hormones will be performed) Serum concentrations of follicle-stimulating hormone, luteinizing hormone, total testosterone and prolactin.Evaluate the level change of oxidative stress biomarkers in Serum (Time frame: Before treatment and after 3 months treatment were finished in 2 treatment arms, oxidative stress biomarkers will be performed) Serum concentrations of Malondialdehyde (MDH) and total antioxidant capacity (TAC) using spectrophotometer at 532 nm.Self-assessment patient’s checklist will be used to assess adherence to treatment. Reasons for dropping out and non-compliance will also be noted and reported.

**Statistics and data-analysis: **Baseline characteristics will be compared between Carob and vitamin E groups using chi-squared tests for categorical variables and independent *t*-test for the normally distributed continuous variables. If the assumptions for normality are violated, then non-parametric techniques will be applied. One-way analysis of covariance (ANCOVA) will be used to evaluate treatment effects of Carob. Relative associations among parameters will be determined by Pearson’s correlation coefficient. All statistical analyses will be conducted using SPSS (Version 16) software. A p-value of less than 0.05 (two-sided) indicates a statistically significant difference, with 95% confidence intervals.

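### Container return is stated for the carob arm only, so adherence, a listed secondary outcome, is not checked or prompted equally in the two arms

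*Protocol article*

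**What the plan says.** The Adherence paragraph of the protocol article sets a self-assessment checklist and adds that "participants will instruct to bring their Carob syrup bottle each visit". The first half names no arm. The second half names one arm's product.

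The Outcome measures section makes adherence an outcome: "Secondary outcome measures will include the change in endocrine parameters, stress oxidative markers and assessment of the adherence to treatment". It then gives the instrument and the handling of non-compliance: "Self-assessment patient’s checklist will be used to assess adherence to treatment. Reasons for dropping out and non-compliance will also be noted and reported". The bottle does not appear in that definition.

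Two other adherence contacts are described without reference to arm. At two weeks, under Intervention, "the patient will received the remaining medications and adherence to treatment will be assessed". Under Follow-up, "To prevent attrition and to assess adherence to treatment, telephone interviews will be conducted again at 2 months from administration of the drug".

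The treatments differ visibly. Under Intervention, "Patients will be assigned (1:1) to receive Carob syrup twice a day or vitamin E", the latter once a day. The Blinding paragraph covers only those who perform and analyse the laboratory assessments.

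**The concern.** A man who has been told to show his bottle at each visit fills in the checklist knowing that his answer could be compared with what is left. He is also reminded of the product each time he prepares for a visit. A man on vitamin E, as the text stands, has no such instruction. Self-report tends to depend on whether the respondent expects to be checked, so the same checklist may not behave in the same way in both arms.

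What is at stake is mainly the reading of the adherence outcome. If reported adherence differs between arms, part of the difference could come from the unequal conditions. If it does not differ, the unequal conditions could have hidden a difference. There is also a possible, weaker effect on behaviour: men are not described as blinded, so an instruction given to one arm could change intake in that arm.

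**Working it through.** No figure in the document bears on this point, so there is nothing to reproduce. The check is a comparison of what the text gives each arm.

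| Element | Carob (30 planned) | Vitamin E (30 planned) | Where stated |
|---|---|---|---|
| Self-assessment checklist | yes | yes | Adherence; Outcome measures |
| Adherence assessed at two weeks | yes | yes | Intervention |
| Telephone interview at two months | yes | yes | Follow-up |
| Instruction to bring the container to each visit | yes | not stated | Adherence |
| Amount remaining measured or recorded | not stated | not stated | – |

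1. **Where the arms match.** Three of the four stated elements carry no arm restriction. Adherence to vitamin E is therefore assessed by the checklist, the two-week assessment and the two-month call.

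2. **Where they differ.** The container instruction names only the carob bottle. It can apply to 30 of the 60 planned men, and to 0 of the 30 on vitamin E. The instruction stands under Adherence and is joined to the checklist by the word also, so its evident purpose is to support the adherence assessment.

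3. **What the bottle is used for.** The document does not say. There are two possibilities.
   - Staff use the bottle to score or correct adherence. The outcome would then be determined differently by arm.
   - Staff only look at it, or do nothing with it. The outcome then rests on the checklist in both arms, but carob men answer it with a possible check in view.

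   The second possibility is closer to the outcome definition, which names only the checklist. Under either, the two arms are not in the same position.

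4. **Direction.** If the instruction raises true intake, it does so in the carob arm. If it makes answers more candid, it lowers reported adherence in the carob arm relative to vitamin E. The two effects pull reported adherence in opposite directions, so neither the sign nor the size of the net effect can be derived from the document.

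**The case against.** The strongest reply is that the outcome definition names a single instrument, the checklist, for all participants. No bottle volume is said to be measured. The statistics section describes no between-arm test of adherence, and non-compliance is only to be noted and reported. The shorter list of secondary outcomes under Intervention leaves adherence out altogether. The shared contacts may already prompt both arms as much as a bottle would. Finally, this is a condensed article, loosely worded at this place, and a matching vitamin E check may stand in the full protocol.

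Much of this stands. A reader might infer that adherence is already measured with different instruments in the two arms. The document does not support that, because the defined instrument is common to both. A reader might also want to attach a percentage-point bias to the adherence comparison. That would require carob men to be scored from returned product and vitamin E men from self-report, which is nowhere stated, and no figure is given from which to derive it.

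The reply does not remove the asymmetry. The point is more than a detail left out: the article does describe container return, and describes it for one product. Adherence is also listed as a secondary outcome of a two-arm trial, so readers will compare the arms on it whether or not a test is planned.

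**Conclusion.** The point holds in a limited form. As written, carob men have an additional potential check and reminder that vitamin E men do not, so checklist answers are collected under different conditions and adherence cannot be read like for like between arms. This rests on taking the Adherence paragraph as it stands, with no vitamin E counterpart in the full protocol.

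Its importance is low. It does not touch the definition of the primary outcome or the sample size. A prompt given only to the carob arm could in principle act on the semen comparison, but nothing in the document shows that it adds much to the shared contacts, and any such effect is unknown and probably small.

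A reader might go further and say that a null result could then be put down to poor vitamin E intake. That does not follow. If vitamin E helps, poor intake weakens the comparator and tends to widen carob's apparent advantage, so it would not explain a null. Nor is vitamin E intake unassessed.

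**What to change.** Replace the second half of the Adherence sentence with an instruction that applies to everyone. For example: *All participants bring their remaining study product (carob syrup or vitamin E) to every scheduled clinic visit. The amount remaining is recorded, and percent taken is computed in the same way in both arms.* For each interval, in either arm:

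percent taken = 100 × (amount dispensed − amount remaining) ÷ amount due to be taken in that interval.

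The amount is volume for the syrup and units for vitamin E, whose presentation the article does not state. Under Outcome measures, name percent taken and the self-assessment checklist together as the adherence measures. If the full protocol already has a vitamin E check, a statement to that effect is enough.

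The occasions exist already: the two-week supply of the remaining medication, the one-month clinic review and the three-month final visit. The cost is one or two sentences and a little staff time per visit. Returned product shows what left the container, not what was swallowed, so the check is imperfect, but equally so in both arms.

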## Methods

**Study design: **The protocol of this randomized controlled trial study has been approved by the Institutional Review Board of Babol University of Medical Sciences (IR.MUBABOL.HRI.REC.1396.179). 

**Study setting: **This study will be conducted at the Infertility and Reproductive Health Center affiliated to Babol University of Medical Sciences and at the urology clinic. 

**Sample size: **The trial is powered to detect an effect size of d ≥0.70 as statistically significant in a two-tailed test with α=0.05 and power of 0.80 with N=26 per condition. As there is the possibility that some patients do not complete the study, we will include 30 patients in Carob and vitamin E groups.

**Participants: **Male partners of couples attending the infertility center of Babol University of Medical Sciences will be included in the study. The proposed sample size is 60 men with teratospermia and oligozoospermia with 30 men in the experimental group taking Carob syrup and 30 men in the comparison group and receiving vitamin E. 

**Eligibility criteria: **The eligibility of each included subject will be confirmed by the urologist. Patients eligible for the trial must comply with all of the following at randomization:

20-45 years of age, who had complained of infertility for at least 12 months, and had no history of surgical or medical treatments for infertility.Having a BMI less than 30.Uncertain oligo-spermatozoa due to WHO criteria (sperm concentration less than 15 million per ml, type A motility less than 25%, and type B mobility Less than 50%, normal morphology less than 15%).Not smoking, drinking alcohol, and addiction to substance. Lack of systemic illness diseases, such as diabetes and thyroid disease, cerebrovascular disease and had no history of chemotherapy.Naturally occurring gonadotropins, testosterone and prolactin 

Lack of history of vasectomy or obstructive azoospermia. Patients with recurrent or residual varicocele, and history of cryptorchidism or Azoospermia and chromosomal abnormalities such as kleinfelter's Syndrome are not enrolled in the study.

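### Three unranked semen parameters form the primary outcome at one 0.05 threshold with no success rule; if any one suffices, the familywise error is up to 14.3%, not 5%

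*Protocol article*

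**What the plan says.** All references are to the protocol article.

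- **Outcome measures** defines the primary outcome in the plural: "The primary outcome measure will be the change in semen parameters after 3 months", carob against vitamin E. It then lists the components: "sperm concentration, 2) percent motility, 3) sperm morphology". The numbering itemises them. Nothing says that it is a testing order or that the first item takes precedence.
- **Intervention** states the aim globally: "The main consequence of the study is to improve the spermogram test". The Methods paragraph of the abstract is equally general.
- **Statistics and data-analysis** gives the test, "One-way analysis of covariance (ANCOVA) will be used to evaluate treatment effects of Carob", without naming the outcome it applies to. It gives one threshold: "A p-value of less than 0.05 (two-sided) indicates a statistically significant difference, with 95% confidence intervals".
- **Sample size** states: "The trial is powered to detect an effect size of d ≥0.70 as statistically significant in a two-tailed test with α=0.05", with power 0.80 and 26 men per arm, raised to 30 for dropout. No semen parameter is attached to the effect size.

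The article describes no hierarchy, alpha split, composite or joint test, and no requirement that all three parameters succeed.

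**The concern.** A primary outcome made of three variables needs a rule that turns three results into one conclusion, and here there is none. With a single 0.05 threshold, the trial could be reported as positive because concentration alone, motility alone or morphology alone crossed it. The 5% would then describe each test but not the trial's main claim.

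The sample size adds to the problem. One effect size at alpha 0.05 fits a single primary variable, yet three are listed and none is identified as the one powered. A reader of the results could not tell which comparison the trial was built to answer.

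The Discussion expects a successful trial to inform urologists' practice, so the error rate attached to success matters.

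**Working it through.** **Inputs from the article:** three primary variables; two-sided alpha 0.05; d = 0.70; power 0.80; 26 per arm, 30 with the dropout allowance; 1:1 allocation. **Assumed, because the article does not give them:** the correlations between the three test statistics (0.3, 0.5, 0.7) and, from step 3 on, no gain from baseline adjustment.

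**1. The plan's own figure.** For one two-sided test, normal approximation:

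n = 2(1.960 + 0.842)² / 0.70² = 32.04, so 33 per arm (t-based: 33.02, so 34).

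The stated 26 does not reproduce. It is what a one-sided 0.05 test needs: 2(1.645 + 0.842)² / 0.70² = 25.2, so 26. Two-sided ANCOVA would also give 26 if the baseline correlation were about 0.43, since 32.04 × (1 − 0.434²) = 26.0, but no correlation is stated. Without that gain, two-sided t-test power at d = 0.70 is 70% at 26 per arm and 76% at 30.

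**2. Familywise error if any one parameter suffices.**

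Independent tests: 1 − 0.95³ = 1 − 0.8574 = 14.3%. For jointly normal two-sided tests this is the maximum whatever the correlation (Šidák inequality). The bound without that assumption is 3 × 0.05 = 15%.

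Simulated equicorrelated two-sided tests (2 million draws each):

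| Assumed correlation | At least one false positive |
|---|---|
| 0 | 14.3% |
| 0.3 | 13.6% |
| 0.5 | 12.5% |
| 0.7 | 10.9% |
| 0.9 | 8.4% |
| 1 | 5% |

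**3. Familywise error if all three are required.** It cannot exceed the error of any single test, so it is at most 5%. Power for all three together cannot exceed the power of the weakest one, so the Sample size statement would not describe this reading either.

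**4. What an alpha adjustment costs.** Holm's strictest step is 0.05/3 = 0.0167. At d = 0.70:

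| Power (two-sided t-test) | 26 per arm | 30 per arm |
|---|---|---|
| One specified parameter, alpha 0.05 | 70% | 76% |
| One specified parameter, alpha 0.0167 | 52% | 60% |
| At least one of three at 0.0167, if all have d = 0.70 (assumed correlations 0.7, 0.5, 0.3) | 71%, 77%, 82% | 78%, 83%, 88% |

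The loss from the adjustment at 26 per arm is therefore 70% to 52% for one specified parameter. The gap between 80% and 70% comes from step 1. If the effect is present on all three parameters, the chance of detecting at least one is no worse than for a single unadjusted test.

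**The case against.** The strongest objection is that the any-one-of-three rule is not in the article. The significance sentence is a generic definition, and the aim of improving the spermogram could mean that every parameter must improve. This stands: the error rates of 11% to 14% are conditional. What remains is that the article fixes neither rule, and its power statement fits neither of them.

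A second objection is that a multiplicity method may sit in a fuller protocol or an analysis plan that is not shown. That is fair for the method itself, and its absence is not the point here. The choice of primary outcome, the threshold and the outcome behind the sample size are stated in this article. An adjustment made elsewhere would not agree with a sample size based on one test at alpha 0.05.

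Three stronger readings are tempting and should not be adopted:

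- A reader might infer a fourth primary variable, because Eligibility criteria separates type A from type B motility. Four independent tests would give 1 − 0.95⁴ = 18.5%. The split appears only for entry, and the outcome list has motility as one item.
- A reader might take 52% power as proof that a hierarchy beats an alpha adjustment. That figure is for one specified parameter. For at least one of three it is about 71% to 82% at 26 per arm, so neither remedy is better on these figures alone.
- A reader might conclude that concentration must be the primary because the men have oligozoospermia. Participants also names teratospermia, and the entry thresholds cover motility and morphology too.

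It is also fair that any choice after the data are seen would be limited to three listed parameters at one time point.

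**Conclusion.** The point holds in conditional form. The article sets three unranked primary parameters against one two-sided 0.05 threshold, gives no success rule, and powers one unnamed outcome. If any single significant parameter supports the claim of benefit, the familywise error is at most 14.3% under independence and about 11% to 14% at assumed correlations of 0.7 to 0.3. A reader might infer that the trial's error rate simply is 14%. The article does not support that, because it never says that one parameter is enough.

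The calculations assume jointly normal test statistics with a common correlation. The power figures also assume d = 0.70 and no covariate gain.

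**What to change.** Before unblinding, amend the Outcome measures, Statistics and data-analysis and Sample size sections, and the registry entry, in one of two ways:

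1. **Keep three primaries.** Use Holm-adjusted p-values and state that benefit may be claimed for any parameter significant after adjustment.
2. **Name one primary**, of the sponsor's choice. Test the other two in a prespecified fixed sequence at two-sided 0.05, stopping at the first non-significant result.

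Under either option, state the success rule and tie the power statement to it. The restated power should start from about 70% at 26 per arm and 76% at 30 for one two-sided test at d = 0.70, or else give and justify the baseline correlation on which an ANCOVA calculation relies.

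**Cost.** Only wording changes, and the design can stay at 60 men if the restated power is accepted. Holm lowers power for a specified parameter at its strictest step to 52% (26 per arm) or 60% (30 per arm). The fixed sequence keeps alpha 0.05 for the first parameter, but the later ones become exploratory if an earlier one fails.

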## Discussion

Over the past decade, diagnosis of male reproductive

performance has progressed dramatically. Many infertile men have disorders treatable with medication that can be eliminated, if properly diagnosed and treated, which will allow natural fertilization. Currently, 60% of the world’s population use herbal drugs for treatment of diseases and 25% of physician’s prescriptions include herbal compounds that have less adverse effects than other drugs. Infertility is one of the medical issues of couples and according to the World Health Organization (WHO), 10% of couples are affected with this problem, of which 10% to 40-50% are related to male factor, the most important is the low quality of sperm. Therefore, paying attention to eliminating these disorders is very important for treatment of couples ‘infertility. There are numerous medicinal herbs with anti-fertility and fertilizing effects in the world. These herbs have been used throughout the history to decrease or increase fertility in men. Many people now use herbal medicines or their derivatives to increase fertility and sexual desire. Thus, it is necessary to study the herbal biologically active substance on male fertility and natural herbal substances with estrogenic and anti-estrogenic properties (5). The WHO has reported that despite the increasing use of herbal medicines, there is still significantly insufficient research information, while the role of articles that examine the herbs is very important. Considering the clarification of adverse effects of chemical drugs on human, women and men have increasingly tended toward using herbal drugs. Herbal drugs are an appropriate substitute for normal drugs.

This is the first study to compare the changes in sperm parameters after two different interventions: the active intervention (Carob) and vitamin E intervention. If successful, this study will provide new knowledge on preferred procedures for helping men and couples to conceive and offer guidance to urologists treating these men.

